# EFFECTIVENESS OF STEROIDS IN PREVENTING UPPER AIRWAY OBSTRUCTION AFTER EXTUBATION IN CRITICALLY-ILL CHILDREN.

Monthly communication newsletter regarding recruitment activity will be sent by email to all researchers. In this newsletter, researchers will also be encouraged to continue recruiting.

Table 1 Modified Taussig score. Upper airway obstruction is considered mild if score is less than 5 points, moderate-severe with  $\geq 5$  points. Modified of Taussig LM. Treatment of Laryngotracheobronchitis (Croup). Am J Dis Child 1975;129:790.

|                     |                        | Score  |                           |                       |                                              |
|---------------------|------------------------|--------|---------------------------|-----------------------|----------------------------------------------|
|                     |                        | 0      | 1                         | 2                     | 3                                            |
| Clinical parameters | Color                  | Normal | Normal                    | Normal                | Cyanotic                                     |
|                     | Air entry              | Normal | Mildly diminished         | Moderately diminished | Substantially diminished                     |
|                     | Retractions            | None   | Mild                      | Moderate              | Severe                                       |
|                     | Level of consciousness | Normal | Restlessness if disturbed | Restlessness at rest  | Lethargy                                     |
|                     | Stridor                | None   | Mild                      | Moderate              | Severe (or no stridor if severe obstruction) |

Table 2. SPIRIT Schedule of Events Timeline: enrolment, assessment of safety, assessment of efficacy, and dispensing of the medicine. Visits 2 to 8, respectively: 15 minutes following extubation, 1 h, 2 h, 6 h, 12 h, 24 h and 48 h after extubation.

|                                                                                                                                            |
|--------------------------------------------------------------------------------------------------------------------------------------------|
| 
EFFECTIVENESS OF STEROIDS IN PREVENTING UPPER AIRWAY OBSTRUCTION AFTER EXTUBATION IN CRITICALLY-ILL CHILDREN.
 |
|--------------------------------------------------------------------------------------------------------------------------------------------|

| Tests                                          | Screening | First visit prior to extubation | Visits 2 to 8 |
|------------------------------------------------|-----------|---------------------------------|---------------|
| Assessment of eligibility               |           |                                 |               |
| Informed consent                               | X         |                                 |               |
| Inclusion and exclusion criteria               | X         |                                 |               |
| Anamnesis                                      | X         |                                 |               |
| Assessment of safety                    |           |                                 |               |
| Physical examination                           | X         | X                               | X             |
| Vital signs                                    | X         | X                               | X             |
| Assessment of adverse events                   |           | X                               | X             |
| Previous and current medications               | X         | X                               | X             |
| Assessment of efficacy a     |           |                                 |               |
| Vital signs                                    | X         | X                               | X             |
| Stridor                                        | X         | X                               | X             |
| Taussig scale                                  | X         | X                               | X             |
| Reintubation                                   |           | X                               | X             |
| Other assessments                       |           |                                 |               |
| Other medications                              |           | X                               | X             |
| Deliveries of medication                |           |                                 |               |
| Randomization and dispensing of the medication |           | X                               | X             |
| Contact with the randomized-dispensing center  | X         | X                               | X             |

## **EVALUATION OF SAFETY**

The occurrence of adverse events from inclusion to study completion will be recorded for all patients. All patients will be monitored until hospital discharge, including those who discontinue their participation in the study. Severe adverse events during hospital stay will be reported to the Study Coordinator and Promotor. In case of occurrence of severe adverse events, follow-up will be performed until remission or until a diagnosis is made and its association with the study medication is established.

A severe adverse event is defined as any adverse event that the patient's treating physician considers to require treatment on the basis of the characteristics and clinical status of the patient. Severe hyperglycemia is any glycemia > 200 mg/dl that persists for more than 6 hours and/or physicians consider to require treatment on the basis of the clinical status of the patient.

Any unused medication will be disposed in accordance with the protocol established by the Pharmacy Unit in collaboration with the Unit of Environmental Management of the Coordinating center, in compliance with ISO 14.001. Upon study completion, any unused or partially used medication will be sent back to the Coordinating Center.

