## **STUDY POPULATION**

The sample will include children between 1 month and 16 years of age admitted to the ICU who require intubation for more than 48 hours, regardless of their condition. Patients with airway malformations, suspected or confirmed croup syndrome, tracheitis or epiglottitis and those who had previously underwent any surgery involving upper or lower airway will be excluded. Furthermore, other exclusion criteria were the administration of steroid therapy within the last seven days, patients who had a previous extubation failure during the stay or refusal to participate in the study.

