## RANDOMIZATION AND MASKING

Patients will be assigned to one of the two therapy groups on a 1:1 ratio by simple randomization using a randomization table on EPIDAT 3.1 (Epidat: software package for epidemiological data analysis. 2006. Consellería de Sanidade, Xunta de Galicia, España; Organización Panamericana de la Salud; Universidad CES, Colombia). The Coordinating Center will send a table for

Protocol number: FIBHGM-ECNC003-2010(FIBHGM-10-01)

|                                                                                                               |
|---------------------------------------------------------------------------------------------------------------|
| EFFECTIVENESS OF STEROIDS IN PREVENTING UPPER AIRWAY OBSTRUCTION AFTER EXTUBATION IN CRITICALLY-ILL CHILDREN. |
|---------------------------------------------------------------------------------------------------------------|

sequential randomization of patients. This table will contain the number of medication that has been assigned to each patient. The treatment group will not be detailed in the randomization table. This table will also include a number of reserve medication for use in case of deterioration, loss, or if the drug is rendered unusable. The Pharmacy Unit of the Coordinating Center will send treatment-arm assignments labeled and blinded as established in the randomization table for each center.

The labeling and blinding of medication kits will be performed by the Pharmacy Unit of the Coordinating Center, which will keep an open record of these kits and their composition. This record will be coded and stored by the pharmacist of the Coordinating Center responsible for the labeling and submission of samples.

In case of severe or unexpected adverse events related to the medication, the Principal Investigator will require the responsible pharmacist to unblind the codes identifying the sample. The Principal Investigator will be informed so that timely action can be taken. The unblinding of any code will be recorded by the pharmacist responsible for sample blinding.

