## **DATA PROCESSING AND AUDITING**

Data from each patient will be collected and anonymized by a study member in a data log. Each study center will send their data logs to the Coordinating Center. The Principal Investigator will enter data from data logs into a single database for all study patients. An interim analysis will be performed by an independent Data Monitoring Committee (DMC) comprised of members of Central Unit of Clinical Research Support and Clinical Trials (UCAICEC) of the Gregorio Marañón Research Institute. The study will only be interrupted if the incidence of UAO or the incidence of severe adverse events is significantly higher in the steroid treatment group as compared to the placebo group. The final analysis will be carried out when the sample size has been reached.

UCAICEC will be responsible for auditing the trial independently from investigators yearly.

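### Severe adverse event is defined by the perceived need for treatment, with no outcome criterion, so reporting and the interim harm comparison mix minor treated events with serious harm and can miss a death

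*Protocol*

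**What the plan says.** Under Evaluation of Safety, the protocol first casts a wide net: "The occurrence of adverse events from inclusion to study completion will be recorded for all patients". It then singles out a severe class: "A severe adverse event is defined as any adverse event that the patient's treating physician considers to require treatment", judged in the light of the child's condition. One event has its own rule: "Severe hyperglycemia is any glycemia > 200 mg/dl that persists for more than 6 hours and/or physicians consider to require treatment". Death, threat to life, prolonged stay and lasting disability are not named as criteria anywhere, and there is no separate serious category.

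Three actions depend on the severe class:

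- **Reporting and follow-up** (Evaluation of Safety): "Severe adverse events during hospital stay will be reported to the Study Coordinator and Promotor". Severe events are also followed until they resolve or are explained.
- **Unblinding** (Randomization and Masking): "In case of severe or unexpected adverse events related to the medication, the Principal Investigator will require the responsible pharmacist to unblind" the sample.
- **Interim harm comparison** (Data Processing and Auditing): the trial is to be "interrupted if the incidence of UAO or the incidence of severe adverse events is significantly higher in the steroid treatment group" than on placebo, and on no other ground.

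The population is children "admitted to the ICU who require intubation for more than 48 hours, regardless of their condition" (Study Population).

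**The concern.** A harm category that feeds a stopping comparison should rank events by what happened to the child. This one ranks them by whether a physician thinks treatment is needed, and it can go wrong in two directions.

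- **Too narrow.** A death or permanent injury for which no treatment is considered required does not meet the definition. It then falls outside the duty to report and outside the severe-event limb of the interim comparison.
- **Too broad.** Any event judged to need treatment qualifies, however minor. In ventilated intensive-care children such events can be expected in both arms. If the comparison counts children, a child already counted for a minor treated event adds nothing when a serious event follows.

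At stake is whether the DMC can see an excess of serious harm on dexamethasone through the one safety comparison that the protocol gives it besides upper airway obstruction (UAO).

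**Working it through.** **1. How the definition sorts events**

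| Event | Severe as written? | Consequence |
|---|---|---|
| Death or lasting injury, no treatment considered required | No | Recorded as an adverse event; no duty to report it as severe; not in the interim severe count |
| Life-threatening event judged to need treatment | Yes | Reported; counts once |
| Minor event judged to need treatment | Yes | Reported; counts once, with equal weight |
| Glucose above 200 mg/dl for over 6 h, no treatment considered required | Meets the hyperglycemia limb, not the general one | Most naturally severe, but the interim rule does not say so |

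**2. The protocol's own figure**

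The definition carries no number. The only planned figure used below is the sample size. Cohen's arcsine method with h = 0.4 gives n = 2 × ((1.960 + 0.842)/0.4)² = 98.1, so 99 per arm. Allowing for 10% loss, 99/0.90 = 110 per arm, as stated under Sample Size.

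**3. Dilution, as an illustration**

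Inputs:

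- From the protocol: 110 per arm, 1:1 allocation, two-sided 5%.
- Assumed, because the documents give no value: serious events s = 2% on placebo and 10% on dexamethasone; background share b of children with at least one treated non-serious event, equal in both arms and independent of s; all serious events counted; an interim at 55 per arm; a pooled Z-test; incidence counted per child.

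Formula: proportion of children with a severe event = 1 − (1 − b)(1 − s). The difference between arms is therefore (1 − b) × 8 percentage points.

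Example with b = 20%: placebo 1 − 0.80 × 0.98 = 21.6%; dexamethasone 1 − 0.80 × 0.90 = 28.0%.

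Power is by exact enumeration of two binomials, rejecting when z > 1.96 in the direction of harm:

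| Background b | Placebo v dexamethasone | Power, 110 per arm | Power, 55 per arm |
|---|---|---|---|
| 0% (serious only) | 2.0% v 10.0% | 74% | 42% |
| 5% | 6.9% v 14.5% | 46% | 25% |
| 10% | 11.8% v 19.0% | 32% | 18% |
| 20% | 21.6% v 28.0% | 19% | 12% |
| 30% | 31.4% v 37.0% | 14% | 9% |
| 50% | 51.0% v 55.0% | 9% | 6% |

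**4. Other harm sizes**

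- Serious events 5% v 15%, 110 per arm: 73% alone, 40% at b = 10%, 26% at b = 20%.
- Serious events 2% v 5%: power is only 20% at 110 per arm and 11% at 55, even with no background at all. A cleaner category does not rescue a small difference.

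**5. What would be lost by replacing the category**

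Suppose dexamethasone raises treated but non-serious events from 10% to 25%, with serious events 2% in both arms and no other background (all assumed). The existing category compares 1 − 0.90 × 0.98 = 11.8% with 1 − 0.75 × 0.98 = 26.5%, and power at 110 per arm is 80%. A serious-only category compares 2% with 2% and signals about 2% of the time, which is its false-positive rate.

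**The case against.** Several points on the other side stand and limit the finding.

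- **The test is a judgment of need, not whether treatment was given.** A reader might infer that any untreated death is excluded. The wording does not support that. A collapse in intensive care would ordinarily be judged to require treatment, even if treatment came too late. The gap is the narrower case in which no treatment is considered required.
- **A death is not lost from the data.** All adverse events are recorded and children are monitored to discharge. An unexpected event related to the medication can still trigger unblinding. What fails is classification as severe, the duty to report, and the place in the interim comparison.
- **The hyperglycemia sentence is not a contradiction.** It reads naturally as a specific limb added to a general rule. It needs only a statement of where it counts.
- **The safety objective does not rest on this category.** The secondary endpoint is the potential secondary effects of dexamethasone. Data Collection and Assessment of Efficacy lists glycemia (when sampled clinically), digestive bleeding and infection as separate variables, and these can be compared without it.
- **The size is assumed throughout.** It is tempting to say that the comparison is swamped, but without a background rate that is inference. At a 5% background, 46% power remains. The protocol also does not say whether incidence means children or events. The calculation applies only per child; in a count of events, the second event would not be lost.
- **The existing category has value.** Step 5 of the working shows that it can detect an excess of treated non-serious effects that an outcome-based category would not see. This argues against replacing it, not against adding to it.

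The core is untouched: the protocol itself fixes the definition, the reporting duty and the interim rule, and none of them refers to outcome.

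**Conclusion.** The point holds in limited form, and the protocol should be changed. The severe category has no outcome criterion, yet it drives reporting, one of the unblinding triggers and one of the two grounds for interrupting the trial. That much follows from the text alone.

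The dilution is conditional. Its direction follows from counting children under an equal and independent background. Its size depends on assumed rates, and the 55-per-arm figures also on an assumed interim. In the main illustration even a 10% background more than halves the power at 110 per arm, from 74% to 32%. The documents do not show what the background is, so they do not establish how much the actual comparison would lose.

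**What to change.** **Evaluation of Safety.** Add a serious adverse event category defined by outcome, whether or not treatment was considered required: death, threat to life, prolonged stay, lasting disability. Make it reportable to the coordinator and promotor. Keep the existing requires-treatment category as a separate recorded item, and state that both hyperglycemia limbs count in it.

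**Data Processing and Auditing.** Keep the existing severe-event comparison. In addition, give the DMC, by arm, the deaths and the proportion of children with at least one serious event. State that the unit is the child, not the event. Because the section now allows interruption on two grounds only, it should also say what role the serious-event comparison plays.

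**Cost.** One more field on the adverse-event form and re-coding of events already reported. There is also one more harm comparison at the interim, which slightly raises the chance of a false safety signal (about 2% for that comparison alone in step 5 of the working). No treated event drops out of the record or out of the present comparison.

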## **SAMPLE SIZE**

The estimated incidence of moderate-severe UAO symptoms is approximately 33% [1–3]. We consider a clinically relevant result the reduction of moderate to severe UAO symptoms incidence by 50% in the treatment group.

To calculate the minimum sample size, a two-sample two-proportion two-tailed comparison test was used, using arcsine approximation for proportions (Cohen's method). To detect a 50% reduction of incidence (0.33 UAO symptoms proportion in the placebo group, 0.16 expected proportion in the treatment group, i.e. Cohen's h effect size=0.4) with 80% statistical power and 5% significance level, 110 subjects per arm will be needed. A follow-up loss rate of 10% has been estimated.

## **STATISTICS**

Categorical variables will be expressed as frequencies and percentages. Normality of continuous data will be assessed by the Kolmogorov-Smirnov test. Continuous variables will be expressed as mean values and SD, or as median values and interquartile range.

To compare the primary endpoint of outcome between the group receiving dexamethasone and the group receiving placebo Z-test statistics will be used. Per protocol analysis will be performed. An intention-to-treat analysis will be also performed to guarantee the effect of randomization.

The association between other categorical variables will be assessed by Chi-squared test or Pearson's coefficient, or by Fisher's exact test, as appropriate, based on the sample size. Continuous variables will be compared by Student's t-test or Mann-Whitney U test. In comparisons of values with respect to time, Student's t-test of repeated measures or Wilcoxon test will be performed, as appropriate. Additional subgroup analysis according to age and pathologies will be performed.

Bilateral statistical tests will be used at a 5% level of significance. Statistical analysis will be performed using SPSS version 20 (SPSS Inc, Chicago, USA).

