## **BACKGROUND**

Critically-ill pediatric patients frequently require endotracheal intubation. Post-extubation upper airway obstruction (UAO) is a common complication that affects up to a third of patients who require endotracheal intubation [1–3].

Laryngeal edema is more frequent and severe in children than in adults due to the small diameter of their airways. Indeed, this type of edema in children affects the subglottal region more frequently than the glottal region [2,4]. Signs of airway obstruction include stridor and respiratory distress, which require reintubation in 6-13% of patients [1–3].

Risk factors related to post-extubation UAO include underlying respiratory or neurological disease, prolonged intubation (more than 36-48h), reintubation, a young age ( $\leq 24$  months of age), or infants weight less than 5 kilograms [1,2].

The obstruction of the upper airways has significant effects on the evolution of the patient. This complication may increase morbidity and mortality, length of hospital stay, duration of mechanical ventilation and healthcare-related costs, especially when the patient requires reintubation [1,2,5,6].

Steroids are one of the most widely used therapies for post-extubation UAO, as they have anti-inflammatory effects, thereby reducing the risk for laryngeal edema and airway obstruction. A range of steroids such as hydrocortisone, methylprednisolone and dexamethasone have been used for the prevention and management of post-extubation UAO [4,7]. Contradictory results have been obtained in studies assessing the effectiveness of steroids in preventing post-extubation UAO [5–10].

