## **METHODS**

### **STUDY DESIGN**

This is a multicentric, prospective, double-blind, randomized, placebo-controlled, phase IV clinical trial. Five pediatric intensive care units of hospitals located in Spain will participate in the study. The study protocol was developed in accordance with the Standard Protocol Items: Recommendations for Interventional Trials (SPIRIT) checklist.

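### The primary Z-test leaves unused the baseline risk factors that the protocol names and collects: a small, nearly free gain in precision is forgone, though the test is valid

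*Protocol*

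**What the plan says.** - **Allocation** (Protocol, Randomization and Masking): "Patients will be assigned to one of the two therapy groups on a 1:1 ratio by simple randomization". No blocking or stratification is stated. Study Design adds: "Five pediatric intensive care units of hospitals located in Spain will participate in the study".
- **Primary test** (Statistics): "To compare the primary endpoint of outcome between the group receiving dexamethasone and the group receiving placebo Z-test statistics will be used". No covariates are named. The same section plans subgroup analyses by age and pathology.
- **Risk factors** (Background): "Risk factors related to post-extubation UAO include underlying respiratory or neurological disease, prolonged intubation". The list continues with reintubation, age up to 24 months and weight under 5 kg. It gives no effect sizes.
- **Data at inclusion** (Data Collection and Assessment of Efficacy): age, weight, one of six diagnostic groups, and days of intubation. Later in the section, the protocol promises that matters affecting the upper airway, with respiratory infection and reintubation as examples, will be accounted for in the analysis. It gives no method.
- **Size** (Sample Size): "0.33 UAO symptoms proportion in the placebo group, 0.16 expected proportion in the treatment group", and "with 80% statistical power and 5% significance level, 110 subjects per arm will be needed".

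**The concern.** Neither the allocation nor the primary test uses variables that the protocol itself regards as prognostic. Subgroup analyses do not repair this: they neither sharpen the overall estimate nor correct it for a chance difference between arms. In a randomised trial, prespecified adjustment for baseline prognostic variables usually does both, at no cost in data. It could matter here because only about 48 primary events are expected and the planned power is 80%, so a result near the significance boundary is quite possible.

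The loose promise to account for airway events raises a second issue. A crude Z-test accounts for nothing, so the two statements do not match. If the promise were later met by adjusting for reintubation, which happens after randomisation and is itself a secondary endpoint, the treatment effect could be biased.

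**Working it through.** **1. The plan's own figure.** Inputs from Sample Size: 0.33 against 0.16, h = 0.4, two-sided 5%, 80% power, 10% loss.

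n = 2(1.960 + 0.842)² / 0.4² = 98.1, rounded up to 99 evaluable per arm; 99 / 0.90 = 110. The stated 110 is reproduced as the figure after loss.

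**2. Power of the unadjusted Z-test at 99 per arm.**

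- Pooled SE, with mean proportion 0.245: √(2 × 0.245 × 0.755 / 99) = 0.0611.
- Unpooled SE: √[(0.33 × 0.67 + 0.16 × 0.84) / 99] = 0.0599.
- Power = Φ[(0.17 − 1.960 × 0.0611) / 0.0599] = Φ(0.84) = 79.9%. At 110 per arm it is 83.9%.

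The plan therefore delivers its stated power without adjustment.

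**3. What adjustment would add.** The protocol gives no covariate effects, so these are assumptions: independent binary factors with equal odds ratios, and prevalences of 50% and 30% (two factors) or 50%, 30%, 30% and 20% (four factors). Each scenario had 198 evaluable children, simple randomisation and 4,000 simulated trials. Monte Carlo error is √(0.8 × 0.2 / 4000) = 0.6 points per figure.

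| Assumed factors | Z-test power | Logistic Wald test | Standardised risk difference |
|---|---|---|---|
| 2, OR 1.5 | 80.4% | 80.2% | 81.2% |
| 2, OR 2 | 79.8% | 81.4% | 82.4% |
| 2, OR 3 | 80.4% | 83.1% | 84.0% |
| 4, OR 2 | 80.0% | 82.3% | 83.2% |
| 4, OR 3 | 80.6% | 85.6% | 86.3% |

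Simulated type I error with both arms at 0.33 was 4.6 to 5.4% for the Z-test, 4.7 to 5.6% for the Wald test and 5.2 to 6.0% for the standardised difference. Part of the last column's advantage may therefore reflect a slightly liberal variance estimate.

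**4. Chance imbalance at 99 per arm.** For a factor with assumed prevalence 50%, the SD of the between-arm difference is √(2 × 0.5 × 0.5 / 99) = 7.1 points. A difference of at least 10 points has probability 16%, and of at least 15 points 3.5%. At 30% prevalence these are 12% and 2%.

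**5. What an imbalance does to the result.** With a marginal risk of 0.33 and prevalence 50%, an odds ratio of 2 means a risk gap of 15.1 points between children with and without the factor; an odds ratio of 3 means 23.5 points. A 10-point imbalance shifts the risk difference by 0.10 × 15.1 = 1.5 or 0.10 × 23.5 = 2.3 points. Against the SE of 6.0 points from step 2, that is 0.25 to 0.39 standard errors.

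**6. Events.** 99 × (0.33 + 0.16) = 48.5.

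**The case against.** The strongest reply is that nothing here is wrong. Simple randomisation followed by a two-sided Z-test is unbiased on average, holds its error rate and matches the two-proportion comparison behind the sample size. An adjusted analysis might also sit in a statistical analysis plan that is not shown. The first part stands in full. The second stands only in part, because the protocol already names the unadjusted test for the primary endpoint, and any later plan would have to be reconciled with it.

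A reader might infer more than the text supports:

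- **That the risk factors are strong.** The Background gives no effect sizes, and with weak factors the gain is close to zero.
- **That the prognostic data are ignored altogether.** Eligibility makes more than 48 hours of intubation universal and excludes previous extubation failure, so two listed factors are largely dealt with by design. Age and pathology are used in subgroups. What remains is age, weight, diagnosis and the spread of intubation duration.
- **That simple randomisation endangers the trial.** A difference of 20 or more among 220 children has probability 20%, but a 100 to 120 split still leaves 83.9% power. The protocol does not say that centre is prognostic. Its mention of a randomisation table for each centre does not change the method, which remains simple randomisation.

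**Conclusion.** The point holds as a modest, nearly free improvement. It is not a flaw that threatens the trial's validity or its planned power. The primary analysis forgoes roughly 0 to 3 points of power if the covariates have odds ratios of 1.5 to 2, and roughly 3 to 6 points if they reach 3. It also leaves a chance imbalance uncorrected. A 10-point imbalance in one factor would matter mainly for a result close to the 5% boundary. All of these sizes rest on assumed odds ratios and prevalences.

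The documents do not support calling the trial underpowered or biased for want of adjustment. The unspecified promise to account for airway events should be settled at the same time, because it does not fit the named test and could be read as licence to adjust for post-randomisation events.

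**What to change.** Before unblinding, amend Statistics as follows.

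- **Primary analysis:** logistic regression on treatment plus a few baseline covariates taken from the inclusion data: age (continuous, or up to 24 months against older) or weight; intubation duration; and diagnosis, collapsed from the six recorded groups. A respiratory yes/no variable cannot be derived cleanly, because the groups record lower airway obstruction but not respiratory disease as such.
- **Duration:** count it to randomisation. The field as worded runs to extubation, which is planned 6 to 12 hours after the first dose.
- **Reporting:** give the standardised risk difference with its 95% CI as the effect measure. Name one test as primary; in the simulation the logistic Wald test stayed closer to 5%. Keep the Z-test as a sensitivity analysis.
- **Model size:** with about 48 events, treatment plus three or four covariate terms leaves 48 / 4 = 12 to 48 / 5 ≈ 10 events per coefficient. Entering all six diagnostic groups (five terms) with treatment, age and duration would leave 48 / 8 = 6. Omit a random effect for centre, whose variance is poorly estimated from five units.
- **Scope:** state that adjustment uses baseline variables only, and say what accounting for airway events means, so that reintubation and other later events stay out of the primary model.

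The cost is a paragraph of text, some programming for the standardised difference and its interval, and the discipline of fixing the covariates in advance. No new data are needed and the randomisation need not change.
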